### Planned statistical analysis

The study team will assess the data collected for all patients at a review meeting to determine the suitability of each patient in the analysis populations prior to breaking the blind for the whole group. AE reporting will be based on the intention to treat population.

### All-available-patient (AAP) population

All patients who have consented for the study will be used for patient accountability and listings and will include patients who are randomised but who do not receive their injection of study medication.

Intent-to-treat (ITT) population: All patients who have been randomised and received their injection of study medication at baseline will be included in an ITT population (missing values will be dealt with using standard procedure in current use). All patients included in the ITT population, who participate in the study, without major protocol violation.

The study team with guidance from a medical statistician and health economist will assess the data collected for all patients at a review meeting to determine the suitability of each patient in the analysis populations prior to breaking the blind for the whole group. AE reporting will be based on the ITT population.

Demographic and background data will be summarised using appropriate summary statistics. Effects of treatment will be estimated using effect size calculations (difference between groups divided by the pooled standard deviation) and 95% confidence interval of the effect size for all continuous variables and odds ratio with 95% confidence intervals will be used for categorical variables (for example, pain).

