### Inclusion criteria to screening phase

• Over 18 years of age.

• Patients admitted to hospital with a diagnosis of stroke (between days 1 and 42) due to a primary cerebral haemorrhage/infarction or subarachnoid haemorrhage producing an upper motor syndrome affecting one body side which results in a hemiplegia.

• Capable of providing informed consent directly or indirectly, or, consent obtainable from next of kin or legal representative.

• No useful arm function (Defined as less than or equal to 2 on the grasp subsection of the ARAT) at onset of spasticity.

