### Outcome measurements

Arm function was measured using the ARAT [8]. The measure will be carried out by a single researcher at baseline, 3 months post injection and 6 months post stroke using the standardised approach advocated by Yozbatriran et al. [9].

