### Measures of spasticity and contractures

Spasticity in the wrist and elbow flexors will be quantified by measuring the muscle activity and stiffness, during an externally imposed stretch of a relaxed muscle. Two stretch velocities will be used. In addition to quantifying spasticity (from the EMG data) and contractures (stiffness) from the data collected during this procedure it will be possible to quantify passive range of movement and the data required to provide a Tardieu Score related to spasticity. A flexible electrogoniometer will be placed on the lateral border across the wrist or elbow - this allows for non-invasive measurement of joint range of movement.

These measurements were taken using the following standardised protocol. Surface EMG electrodes will be placed in accordance with European recommended sites for the biceps and long head of triceps [10].

The electrodes will be placed on the forearm flexor and extensor muscles using bony landmarks to identify location as follows:

Forearm flexor muscles - In a line between the medial epicondyle of the humerus and medial border of the biceps tendon - from the mid-point of this line the electrodes will be attached approximately one-third of the length of the forearm. With the arm in full pronation the electrode is placed one-third of the distance between the lateral epicondyle of the humerus and the radial styloid.

The therapist will move the joint from full flexion to full extension, using two manually controlled velocities, a maximum of six times. The data will be collected using a DataLog (Biometrics Ltd.). Following transfer to a computer, the data will be interrogated to produce measurements of spasticity and joint stiffness. Patient position will be uniform at all measurements. This measurement protocol has been used in previous trials [11,12].

These measures will be taken at baseline, 2, 4 and 6 weeks and 3 months post injections and finally at 6 months post stroke.

Pain will be measured using a visual analogue scale at baseline, 3 months and 6 months.

Muscle function will be quantified by measuring isometric strength at mid-range of movement using a dynamometer. A grip dynamometer will measure grip strength. (Fatigue will be derived from the above measurement of strength by estimating the time taken for the force generation to drop to 70% of the maximum isometric strength measurement). These measures will be taken at baseline, 3 months and 6 months.

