The Barthel index will be measured at baseline, 3 months and 6 months [13]. While it was originally devised to assess the individual’s capacity to carry out physical tasks, it has subsequently become used as a measure of activity.

Measure of quality of life using the EuroQuol EQ5D will be taken at 3 and 6 months. The EuroQuol EQ-5D-5 L is a health-related measure of quality of life measuring five dimensions: mobility, self-care, usual activities, pain/discomfort and anxiety/depression. While the similar but older version (5D-3 L) with just three levels of problem has been used extensively in stroke, the newer version with five levels has been used less so.

A measure of care giver burden will be taken at 6 months using the Care Giver Strain Index (CGSI) as will the modified Rankin scale. The CGSI was first developed by Robinson (1983) and has been used widely with stroke survivors’ families and carers [14].

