### Sample size calculations

Sample size calculations have been identified using data from a pilot study [12]. With an effect size of 0.5 and at 80% power (0.05) significance level 126 patients will be required. With an effect size of 0.6 and at 80% power (0.05) significance level 88 patients will be required. Allowing for an attrition of 20% the maximum number of participants we will need is 150 and the minimum is 88.

All available patients who have consented for the study will be used for patient accountability and listings and will include patients who are randomised but who do not receive their injection of study medication.

All patients who have been randomised and received their injection of study medication at baseline will be included in an ITT population (missing values will be dealt with using standard procedure in current use).

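### The stated effect estimate for continuous outcomes names no baseline adjustment although baselines are collected; it is valid but less precise than it could be, probably by little for ARAT

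*Protocol article*

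**What the plan says.** The last paragraph under the All-available-patient population heading of the protocol article fixes the estimator: "Effects of treatment will be estimated using effect size calculations (difference between groups divided by the pooled standard deviation". It applies to all continuous variables and comes with a 95% confidence interval. Categorical variables get odds ratios, and pain is the example given. No covariate, change score or model is named.

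The measurement sections show which baselines exist:

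- **ARAT (primary outcome):** "The measure will be carried out by a single researcher at baseline, 3 months post injection and 6 months post stroke".
- **EMG, stiffness and passive range:** "These measures will be taken at baseline, 2, 4 and 6 weeks and 3 months post injections and finally at 6 months post stroke".
- **Strength and fatigue:** baseline, 3 months and 6 months, in the same section.
- **Barthel:** "The Barthel index will be measured at baseline, 3 months and 6 months".

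Two further facts matter. The entry rule restricts the ARAT baseline: "No useful arm function (Defined as less than or equal to 2 on the grasp subsection of the ARAT". Patients may also enter between day 1 and day 42 after stroke, so time from stroke to randomisation varies. The randomisation section describes permuted blocks and names no stratification factor.

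**The concern.** A difference divided by a pooled SD, read as written, uses only follow-up values. Baseline severity and time since stroke are recorded but not used. Two things follow.

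- **Precision.** Where baseline predicts follow-up, the interval is wider than the data require. Adjustment would recover that precision without recruiting another patient.
- **Interpretation.** The primary objective concerns arm function on the ARAT, but the only summary promised is in SD units. Patients start near the floor, so the follow-up SD depends on how many leave it. The same gain in points can then give a different effect size. A clinician cannot turn the result back into ARAT points without the SD.

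**Working it through.** **Step 1: reproduce the plan's own figures.** The Sample size calculations section states "With an effect size of 0.5 and at 80% power (0.05) significance level 126 patients will be required", and 88 for an effect size of 0.6. Sidedness and allocation ratio are not given; two-sided 0.05 and 1:1 are assumed. Per arm, n = 2(1.960 + 0.842)²/d².

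- d = 0.5: 62.8, rounded up to 63, total 126.
- d = 0.6: 43.6, rounded up to 44, total 88.

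Both match, and they rest on an unadjusted comparison. A one-sided test would give 100 and 70, which does not match.

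**Step 2: completers after the stated 20% attrition.** 150 × 0.8 = 120, and 88 × 0.8 = 70.4, taken as 70.

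**Step 3: effect of adjustment.** With correlation r between baseline and follow-up, the ANCOVA residual variance is about (1 − r²) times the unadjusted variance. Power is that of a two-sample test at d/√(1 − r²). The article gives no r, so a range is shown. Each cell gives the t-test result, then the normal approximation.

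| Assumed r | Variance saved | 120 completers, d = 0.5 | 70 completers, d = 0.6 |
|---|---|---|---|
| 0 | 0% | 77.5% / 78.2% | 69.7% / 70.9% |
| 0.2 | 4% | 79.2% / 79.8% | 71.4% / 72.6% |
| 0.3 | 9% | 81.3% / 81.9% | 73.7% / 74.9% |
| 0.5 | 25% | 88.0% / 88.5% | 81.5% / 82.6% |

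Example, r = 0.3 and 120 completers: 0.5/√0.91 = 0.524. The normal approximation is then Φ(0.524 × √30 − 1.960) = Φ(0.911) = 81.9%.

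**Step 4: which rows apply to which outcome.** The ARAT entry rule compresses the baseline range, which tends to lower its correlation with later ARAT. The rows at 0.2 and 0.3 are therefore the more plausible ones for the primary outcome, a gain of roughly 2 to 4 percentage points. Stiffness, strength and Barthel have no such restriction written into the entry criteria, so r = 0.5 is conceivable for them. At that value the confidence interval narrows to √0.75 = 0.87 of its unadjusted width.

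**The case against.** The strongest reply is that the article defines a scale and not a model. The difference that is divided by the SD could be an adjusted one, and a condensed article may leave covariates to an analysis plan that is not shown. That stands in part: the text does not exclude adjustment. But it does more than stay silent. It names a method for all continuous variables, and taken at its word that method is unadjusted.

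The second reply is that nothing is invalid. This stands in full. Under randomisation the unadjusted difference is unbiased, and its 95% interval already allows for chance imbalance. The effect-size scale also matches the way the trial was sized, and the text does not forbid reporting ARAT points as well.

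Some stronger readings are tempting but not supported:

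- **The unadjusted analysis makes the trial underpowered.** With 120 completers and effect size 0.5, power is about 78%, close to target. The clear shortfall is at the minimum of 88, which carries no attrition allowance. That is a separate sample-size matter, and at r = 0.2 to 0.3 adjustment would not restore 80% there.
- **Pain is handled the same way.** The article names pain as a categorical variable, analysed by odds ratio.
- **EQ-5D needs a baseline.** It is listed without one ("Measure of quality of life using the EuroQuol EQ5D will be taken at 3 and 6 months"), but a randomised comparison at follow-up does not require it, and its timing has no bearing on this estimator.

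**Conclusion.** The point holds as an improvement to a stated estimator, not as an error in it. Baselines that the trial already collects are not used in the analysis as written. For ARAT the likely loss is small: 4% to 9% of variance if r is 0.2 to 0.3. For stiffness, strength and Barthel it may be larger, 25% at r = 0.5.

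These sizes rest on assumed correlations, on 1:1 allocation, on a two-sided 0.05 test and on 20% attrition. The documents also give no figure for how strongly days since stroke or baseline Barthel predict later ARAT, so any extra gain from those covariates is unquantified. The case for reporting in ARAT points does not depend on r.

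**What to change.** State that ARAT will be analysed by ANCOVA on treatment arm and baseline ARAT, with days from stroke to randomisation and baseline Barthel as prespecified covariates. Report the adjusted difference in ARAT points with a 95% confidence interval, robust or bootstrap because scores start near the floor. Keep the standardised effect size as a supplement. Analyse the other continuous outcomes that have a baseline (EMG, stiffness, range, strength, fatigue, Barthel) in the same way, each with its own baseline.

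The wording should be settled before the blind is broken, so that covariates are not chosen after seeing results. The cost is a change of analysis text and a little more analysis work. It needs no new patients, visits or measurements.

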#### Secondary objectives

1. To evaluate the effectiveness of BoNT-A and physiotherapy when compared with placebo and physiotherapy in patients with focal spasticity, post stroke, identified on clinical and neurophysiological grounds.

2. To reduce focal spasticity in the arm as measured by surface EMG response of the wrist and elbow flexors to an externally imposed perturbation.

3. To improve strength and fatigue as measured by maximum isometric strength and the rate of force production in the wrist and elbow joints.

4. To reduce stiffness and increase passive range of movement by measuring the range of movement and force required to produce the movement with a custom built device.

5. To reduce post-stroke pain measured using a visual analogue scale.

6. To improve quality of life (using the EuroQol Group EQ5D) and assess care giver burden (using the Care Giver Burden Scale).

7. To reduce the need for additional oral anti-spasmodic drugs or additional botulinum treatment during the course of rehabilitation.

8. To reduce long-term costs (quantified using resource utilisation diaries) and identify discharge destination.

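### Pain is collected as a visual analogue scale score, but the analysis text names it as its example of a categorical variable to be analysed by odds ratio

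*Protocol article*

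**What the plan says.** Three places in the Protocol article bear on this.

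- Secondary objectives, item 5: "To reduce post-stroke pain measured using a visual analogue scale".
- Measures of spasticity and contractures: "Pain will be measured using a visual analogue scale at baseline, 3 months and 6 months".
- The effect-size paragraph under the All-available-patient (AAP) population heading sets two rules. Every continuous variable gets an effect size, defined as the "difference between groups divided by the pooled standard deviation", with a 95% confidence interval. For the rest, an "odds ratio with 95% confidence intervals will be used for categorical variables (for example, pain"). Pain is the only outcome that this paragraph names under either rule.

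One other pain item is collected. The EQ-5D-5L, at 3 and 6 months, covers "mobility, self-care, usual activities, pain/discomfort and anxiety/depression", each on five levels.

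**The concern.** A VAS yields a numeric score. By the article's own two rules it belongs with the continuous variables, yet it is named as the example of the other kind. The objective and outcome sections cannot be followed together with the analysis paragraph unless the score is first converted into categories, and the article states no conversion.

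Two things are at stake. Coarsening a score that has already been collected usually costs precision. And an odds ratio for being in a pain category answers a different question from the one in objective 5, which concerns a reduction in pain on the scale itself.

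**Working it through.** **1. The passages side by side.** Instrument: VAS (objective and outcome sections agree). Time points: baseline, 3 and 6 months. Assigned method: odds ratio, as a categorical variable. Method assigned to continuous variables: standardised mean difference. The instrument and the assigned method do not match.

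**2. Could the analysis paragraph mean the EQ-5D pain item?** That item is ordinal, so an odds ratio would suit it. But the paragraph does not mention the EQ-5D, the item is one dimension of the quality-of-life measure, and objective 5 is tied to the VAS. This reading does not remove the mismatch.

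**3. The plan's own figures.** The article gives none for pain. Its sample sizes are general: "With an effect size of 0.5 and at 80% power (0.05) significance level 126 patients will be required" and "With an effect size of 0.6 and at 80% power (0.05) significance level 88 patients will be required". With 1:1 allocation, two-sided alpha 0.05 and the normal approximation, n per arm = 2(1.960 + 0.842)²/d² = 2 × 7.849/d².

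- d = 0.5: 15.698/0.25 = 62.8, so 63 per arm and 126 in total.
- d = 0.6: 15.698/0.36 = 43.6, so 44 per arm and 88 in total.

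Both reproduce. That section does not mention pain.

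**4. Information kept by one binary cut.** Assumption, not from the article: a normal VAS with equal SDs. For a cut with a fraction q on one side, efficiency relative to the mean difference is φ(z_q)²/[q(1 − q)].

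| Split | φ(z_q) | Efficiency | Loss |
|---|---|---|---|
| 50/50 | 0.399 | 0.159/0.25 = 0.637 | 36% |
| 30/70 | 0.348 | 0.121/0.21 = 0.576 | 42% |
| 20/80 | 0.280 | 0.0784/0.16 = 0.490 | 51% |

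More extreme cuts lose more: 57% at 15/85 and 66% at 10/90.

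**5. Information kept by an ordinal odds ratio.** Same assumption, k equal-sized categories with rank scores. Efficiency is cov²/var, where cov is the sum of score times the drop in φ across each category, and var is the variance of the scores.

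- k = 3: 0.2424²/0.0741 = 0.793, a loss of 21%.
- k = 5: 0.2665²/0.0800 = 0.888, a loss of 11%.

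**6. Illustration in power terms.** This borrows d = 0.5 from the general sample size, because no effect is stated for pain. With 63 per arm the continuous comparison has 80% power. Suppose half of controls lie above the cut. Then the treated proportion above it is 1 − Φ(0.5) = 0.309. The two-proportion formula with pooled null variance gives 102 per arm for 80% power, and 59% power at 63 per arm. With 30% or 20% of controls above the cut, power at 63 per arm is 51% or 42%.

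**7. A case that goes the other way.** Assume 60 per arm, any pain in 60% against 35%, and Beta(2,2) scores among those with pain, so that treatment changes only whether pain is present. Simulated power is about 80% for an any-pain split, about 65% for the t test and a little over 70% for the rank test. This too is an assumption, chosen to favour the split.

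**The case against.** The best defence has four parts.

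*The loss is not a fact about this trial.* This stands. The figures in steps 4 to 6 depend on normality, on the number and position of the cuts, and in step 6 on a borrowed effect size. Patients enter within 42 days of stroke and no pain criterion is listed, so many zero scores are possible, and step 7 shows that splitting can then do better than a mean comparison.

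*An odds ratio does not require a single cut-point.* This stands. The article says categorical, not binary, and a proportional-odds model over several categories also gives an odds ratio. What is required is some set of categories.

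*Missing categories and missing baseline adjustment are details for the full protocol or analysis plan.* This stands as well. A reader might infer that the cut will be chosen after the data are seen, or that the baseline VAS will go unused. The article supports neither inference: it is a condensed text, and it mentions baseline adjustment for no outcome, including the primary one.

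*Deleting the example would be enough.* It would remove the contradiction, because VAS pain would then fall under the existing continuous rule. Adjustment and a robustness check are improvements beyond that.

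None of this touches the mismatch itself. The article states a method for a named outcome, and that method does not fit the outcome as the article defines it. More detail elsewhere could define categories, but the published rule would still coarsen a collected score.

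**Conclusion.** The point holds as an internal contradiction: pain is defined as a VAS score and assigned the categorical analysis. It is a stated rule that fits its outcome badly, not an omission.

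Its size is conditional. Under a roughly normal VAS, one cut between 50/50 and 20/80 loses about 36% to 51% of the information; three to five equal ordered categories lose about 21% to 11%. A reader might conclude that the plan throws away a third to a half of the pain information. The article does not support that as a flat statement, because it gives no distribution, no cut-point and no number of categories, and a zero-heavy score could reverse the comparison.

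The consequences are limited. Pain is one of several secondary outcomes and the sample size section does not refer to it. It should be corrected, but it does not threaten the primary analysis.

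**What to change.** In the effect-size paragraph, delete the parenthetical example that names pain. Analyse VAS pain at 3 and 6 months under the continuous-variable rule: a between-group difference with 95% confidence interval, adjusted for the baseline VAS already collected. Add a rank-based or bootstrap check, because the scores may be skewed or contain many zeros.

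Keep odds ratios for outcomes that are categorical as collected, such as discharge destination and the modified Rankin scale. If a categorical pain analysis is also wanted, make it supplementary and fix its categories before unblinding.

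The cost is a sentence or two of analysis text. No extra data or visits are needed, and the sample size does not change.

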### Sample size calculations

Sample size calculations have been identified using data from a pilot study [12]. With an effect size of 0.5 and at 80% power (0.05) significance level 126 patients will be required. With an effect size of 0.6 and at 80% power (0.05) significance level 88 patients will be required. Allowing for an attrition of 20% the maximum number of participants we will need is 150 and the minimum is 88.

All available patients who have consented for the study will be used for patient accountability and listings and will include patients who are randomised but who do not receive their injection of study medication.

All patients who have been randomised and received their injection of study medication at baseline will be included in an ITT population (missing values will be dealt with using standard procedure in current use).

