### Randomisation method

Randomisation was by computer-generated random permuted blocks in a pseudorandom sequence.

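### The recruitment range of 88 to 150 does not contain the 20% attrition allowance it claims: the minimum has none, and the maximum is slightly short

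*Protocol article*

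**What the plan says.** The Sample size calculations section of the protocol article makes three statements.

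- For the smaller effect: "With an effect size of 0.5 and at 80% power (0.05) significance level 126 patients will be required".
- For the larger effect: "With an effect size of 0.6 and at 80% power (0.05) significance level 88 patients will be required".
- For recruitment: "Allowing for an attrition of 20% the maximum number of participants we will need is 150 and the minimum is 88".

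The first two do not mention attrition. It appears only in the third, where it introduces both the maximum and the minimum. Nothing else in the article explains how 150 or 88 was reached.

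**The concern.** One number cannot be both the requirement before losses and the requirement after allowing for 20% losses, yet 88 is given as both. The maximum also looks low, because 20% off 150 leaves 120, which is fewer than the 126 said to be needed.

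What is at stake is the power claim. The lower end of the range is the number at which recruitment could reasonably be called sufficient. A trial that ends there, with the attrition the article itself expects, would be reported as designed for 80% power when it had about 70% at the more optimistic of its two planning effects.

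**Working it through.** **Inputs from the protocol article**

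- Standardised effects 0.5 and 0.6, 80% power, significance level 0.05, 20% attrition and the range 88 to 150 (Sample size calculations).
- The effect size is the "difference between groups divided by the pooled standard deviation" (analysis text under All-available-patient (AAP) population), so the SD is 1 on this scale.

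**Assumptions not stated in the article**

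- Two-sided test. One-sided calculations give 100 and 70, which do not match.
- 1:1 allocation. The Randomisation method section mentions permuted blocks but no ratio.
- Lost patients contribute no outcome data.
- The range counts randomised patients.

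**Step 1: reproduce the base figures.** With n per arm = 2(1.96 + 0.8416)² / d²:

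- d = 0.5: 62.8, rounded up to 63 per arm, 126 in total. This matches.
- d = 0.6: 43.6, rounded up to 44 per arm, 88 in total. This matches.

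The t-test version gives 128 and 90, close enough that the base figures are not in question. The fault lies in the attrition step.

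**Step 2: apply 20% attrition.** The correct inflation is N / (1 − 0.20). The common shortcut is N × 1.2.

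| Effect | Before losses | N / 0.8 | N × 1.2 | Article |
|---|---|---|---|---|
| 0.6 | 88 | 110 | 105.6, so 106 | 88 |
| 0.5 | 126 | 157.5, so 158 | 151.2, so 152 | 150 |

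The minimum fits neither rule. The maximum is close to the shortcut, rounded down. It covers 1 − 126/150 = 16% attrition.

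**Step 3: power after 20% loss.** The normal approximation is Φ(d√(n/2) − 1.96), with n per arm. The t figures come from the noncentral t distribution.

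- 88 randomised: 88 × 0.8 = 70.4 evaluable, 35.2 per arm. At d = 0.6, 0.6 × √17.6 − 1.96 = 0.557, so power is 71.1% (t: 69.9%).
- 150 randomised: 150 × 0.8 = 120 evaluable, 60 per arm. At d = 0.5, 0.5 × √30 − 1.96 = 0.779, so power is 78.2% (t: 77.5%). At d = 0.6 it is 90.8% (t: 90.3%).

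**Step 4: detectable effect at the minimum.** With 35.2 per arm, the effect detectable with 80% power is 2.8016 × √(2/35.2) = 0.67 (about 0.68 by t). That is larger than either planning value. At d = 0.5 the same 35.2 per arm give 55.5% (t: 54.3%), although the article does not pair 88 with that effect.

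**The case against.** The best defence reads the sentence as a worst case and a best case: 150 for the smaller effect with losses, 88 for the larger effect without them. The fault would then be loose wording. This is possible, but the attrition clause introduces both numbers, and on this reading 88 still leaves no room for the losses the article expects.

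A second argument is that a one-sided calculation gives 70/0.8 = 87.5, or 88. This fails because the article gives 88 as the figure before attrition, and 126 is reproduced only by a two-sided test.

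Other points carry some weight and limit the finding:

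- The shortfall at 150 is 8 patients and about 2 points of power. It would not justify a correction on its own.
- The article does not claim 80% power for 88 patients at an effect of 0.5, so the figure of about 55% contradicts nothing it says.
- No text makes 88 a stopping point. The Trial status section gives only recruitment dates.
- The planned analysis is estimation with 95% confidence intervals, so the precision achieved will be visible in the results. At the minimum, the approximate half-width for the effect size, 1.96 × √(4/N), goes from 0.42 SD with 88 evaluable to 0.47 SD with 70.
- Injected patients stay in the intention-to-treat population with missing values handled in some way, so 70 evaluable is the pessimistic end.

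These points bear on how much the error matters. None makes the sentence correct, since the section justifies its numbers by power.

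**Conclusion.** The concern holds: the sentence is wrong as written. The pre-attrition figures of 126 and 88 are sound, but the range said to allow for 20% attrition does not do so.

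The material fault is the minimum. It is 22 short of the 110 needed (110 − 88), and power at an effect of 0.6 falls from 80% to 70–71%. The maximum is 8 short of 158, with power at 0.5 of 77.5–78%; this is minor, but it comes from the same step.

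The power figures rest on the four assumptions listed in the working. The internal contradiction over 88 needs none of them.

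**What to change.** Correct the paragraph in one of two ways.

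1. **Restate the numbers.** 88 evaluable patients (effect 0.6) require 110 randomised, and 126 evaluable (effect 0.5) require 158 randomised, allowing for 20% attrition. If t-test base figures of 90 and 128 are preferred, the totals are 113 and 160. With the normal-approximation figures, this adds 22 patients at the lower end and 8 at the upper.
2. **Keep 88 to 150 and restate the power.** After 20% loss, 88 randomised give about 70% at an effect of 0.6, and 150 randomised give about 78% at 0.5. If 88 was meant as a no-loss figure, say so beside the power. This needs no extra patients; the cost is one paragraph and a less favourable stated power.

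In either case, state the two-sided test and the 1:1 allocation, if these were used, so that the calculation can be reproduced.
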